### **3. Study Procedures**

#### **5.1 Study Design**

**5.1.a. ASAP Overview** The ASAP project will be conducted as a Hybrid Type I, randomized, stepped-wedge trial at 6 intervention sites and 30 control sites over a 3.5-year period (Figure 1). The 6 intervention sites will begin the 21-month active implementation period; (orange shading for WAVE 1, green shading for WAVE 2 and yellow shading for WAVE 3) in 3 staggered “steps” with 2 sites per step. Immediately following the active implementation phase for WAVES 1 and 2 will be a sustainability phase up to 7 months in duration (purple shading). WAVE 3 will not have a sustainability phase. This design allows for 3 active implementation data periods of 7-months duration for each WAVE. As seen in Figure 1, there are a variable number of 7-month data periods in the baseline and the sustainability periods by wave. The ASAP quality improvement intervention includes a systems redesign Virtual Collaborative and data monitoring. As part of the quality improvement intervention, sites will locally tailor and implement an ASAP approach, in which each site chooses a diagnostic strategy from a menu that includes unattended PSG, in-laboratory PSG, or direct to auto-PAP approach. Similarly, sites may choose any treatment strategy.

Figure 1. ASAP Project Active Implementation and Sustainability Timeline

[figure not shown]

**5.1.b. Participating Sites** To be eligible for inclusion in ASAP a site had to have >50 stroke/TIA patients per year and have at least 1.0 FTE staff dedicated to systems redesign. The sites were chosen because they are diverse in terms of geography and sleep infrastructure. Data regarding the capacity to perform acute OSA assessment at each site is included in site investigators' letters of support. Furthermore, the sleep clinical champions vary across the sites and include clinicians trained in pulmonary, neurology, and psychiatry; some have on-site sleep laboratories whereas others use unattended PSG or fee-basis for their PSGs.

Table 2 data provide the estimates that were used in the revised power calculations: 111 patients per year will be eligible.

| VAMC (Site)       | Annual Patient Volume (n) a | History of OSA (n) | PSG in prior 5-years (n) | Potentially Eligible (n) b |
|-------------------|----------------------------------------|--------------------|--------------------------|---------------------------------------|
| A                 | 212                                    | 30                 | 18                       | 172                                   |
| B                 | 150                                    | 26                 | 17                       | 111                                   |
| C                 | 169                                    | 52                 | 20                       | 107                                   |
| D                 | 157                                    | 30                 | 23                       | 116                                   |
| E                 | 141                                    | 37                 | 37                       | 92                                    |
| F                 | 172                                    | 39                 | 32                       | 117                                   |
| National average  | 158.2                                  | 37.3               | 25.4                     | 107.5                                 |
| ASAP sites | 157.3                           | 35.2        | 20.3              | 119.2                          |

aAnnual stroke/TIA volume based on FY2017 data and excludes patients with a history of OSA. bPotentially eligible patients exclude those with: history of OSA, PSG in prior 5 years, death within 7-days of discharge, and hospice referral.

**5.1.c. Intervention Description** The quality improvement intervention will include: a systems redesign Virtual Collaborative and data monitoring.

**Systems Redesign Virtual Collaborative** A Virtual Collaborative will be convened among the investigators and the clinical team members from the active implementation sites. The site clinical teams will include members from the stroke team, sleep medicine, and systems redesign. The Virtual Collaborative will be used to develop system redesign approaches to overcome barriers to

implementation, share lessons and resources across sites, and foster a sense of community around stroke and sleep care. The Virtual Collaborative will be conducted using a virtual kick-off event, followed by monthly video-teleconferencing. As part of the kick-off event, [name], a Lean Six Sigma-trained Black Belt, will lead a mini-rapid process improvement workshop (RPIW). The site teams will: (1) map the local current value stream; (2) facilitate team problem solving; (3) design an achievable future state process map (including the specific approach to diagnosis and treatment that will be used at the site), and; (4) begin early discussions regarding sustainability of the intervention. Define, Measure, Analyze, Improve, and Control (DMAIC) is a prescribed improvement process for Systems Redesign/Lean Six Sigma methodology which focuses on identifying and defining root causes of a problem prior to applying solutions, implementing solutions linked to an underlying cause, and then establishing best practices to assure that an intervention is effective and sustainable. DMAIC utilizes such techniques as process mapping, PDSA matrices, and Failure Modes and Effects Analysis (FMEA). Together, these approaches help staff systematically identify and remove non-value-added work to the process and develop breakthrough projects which remove defects in the process.

ASAP will leverage an existing national platform called the Integrated Operations Platform (IOP), which includes several components that can be used for service planning; it is a web-based tool that is openly accessible (no passwords required). The IOP has successfully fostered collaborations across VAMCs. It has provided a platform for VA leadership to identify best practices and “push” strategies. The IOP hub provides a dynamic learning environment that supports the theme of promoting a learning healthcare system. The IOP hub will serve the ASAP project as a connectivity hub for investigators, site PIs, systems redesign personnel, and VHA operational partners. Resources including staff education materials, articles, protocols, and project charters will be shared in the library.

We will utilize VA Research Electronic Data Capture (REDCap) database monthly reflection survey, the Prospectively-Reported Implementation Update and Score (PRIUS), data collected from monthly ASAP Collaborative Calls (e.g., triumphs, barriers, and goals reported by sites, field memos), to obtain monthly updates on site specific processes and procedures, which will then be used by the ASAP Implementation Team to inform External Facilitation with the sites while promoting the development of a broader ASAP Community of Practice across sites. Active intervention site team members will participate in monthly collaborative virtual conference calls. During these calls, sites will share lessons learned as they implement the action plans that were developed during the kick-off, brainstorm together about overcoming barriers to ASAP implementation, review interim data, and support likeminded VHA staff/providers who are all working to improve care and outcomes for Veterans with stroke/TIA. Study staff will take notes during the call. Furthermore, sites will submit slides regarding what has worked well during the last month (i.e., facilitators), areas of improvement (i.e., barriers), and goals for the upcoming month. Information collected during the calls will be used by the Implementation Team to inform

future External Facilitation calls and discussions related to CFIR constructs and GO score scoring. Text from the PRIUS calls, ASAP collaborative calls, External Facilitation call interactions, will be uploaded to NVivo for analysis by the team.

**Data Monitoring** Chart review will be conducted centrally (Indianapolis VAMC/West Haven VAMC) and at the local sites. Chart review will be conducted on all eligible ischemic stroke and TIA patients who are admitted at the participating sites. Patients with ischemic stroke/TIA will be identified using ICD-10 codes in the Corporate Data Warehouse (CDW). The hub will include facility-level data for: OSA diagnosis and ASAP primary and secondary effectiveness outcomes. The hub allows sites to compare their data to other sites and to examine trends over time. Site staff/providers will use these data to iteratively improve ASAP implementation. For example, if sites learn that OSA testing rates are lower after discharge than during the hospitalization period, processes focusing on hospitalized (rather than discharged) patients would be appropriate. To complement data seen on the Hub, the results of the chart review will be provided to implementation sites and will be discussed at the Virtual Collaborative monthly conferences. Furthermore, recognizing that each patient is an opportunity to improve local ASAP processes and procedures, during external facilitation sessions, patient-level data will be reviewed with the sites.

**5.1.d. Implementation Strategy** This project draws explicitly upon the implementation strategies of external facilitation and data and feedback, which will be assessed on an ongoing basis over the intervention period.

**External Facilitation** External facilitation changes over time based on the needs of the team. However, the core elements of relationship-building, methods training, communication, facilitating team-based problem solving, and monitoring performance over time will be preserved through external facilitation from a Lean Six Sigma Black Belt experienced in stroke QI work and ASAP investigators experienced in implementation of post-stroke/TIA OSA programs.

**Audit and Feedback** As described above, active implementation sites will receive monthly feedback on quality indicators for ASAP-related process and outcome data. To support the sites' use of data, the local teams will receive explicit training in team-based reflecting & evaluating, goalsetting, and planning. Meeting as a group, local teams will be encouraged to formally ask and answer questions like: "How are we doing?" "Are we where we want to be?" "What performance goals do we want to set as targets?" "What do we need to do to achieve our goals?" "How will we know how far or how close we are to hitting our targets?" The audit and feedback implementation strategy is a key element of the ASAP approach to sustainability, as the activities of reflecting & evaluating, goal setting and planning allow local teams to engage in continuous improvement, stepping back as a group on a periodic basis to review data related to the trajectory of their progress over time, make adjustments as needed to address any dips in performance, and consider how to sustain improvement. Hub usage data will also be collected and summed by site in order to determine how often each month the hub is accessed by each site to audit their own performance.

**5.1.e. Site Randomization** As described above, the ASAP study will be conducted as a stepped-wedge trial with six sites randomly allocated to receive the intervention in three steps, two facilities at a time. At the start of the study, the order in which sites will receive the ASAP program will be derived from a computer-generated randomization list created by ASAP senior statistician ([name]).

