## **6. Communication Plan**

[name], in conjunction with VA Connecticut Healthcare System and Richard L. Roudebush VAMC ASAP staff, will communicate with the Local Site Investigators (LSIs) and site-based ASAP staff regarding obtaining local site approvals. Staff within the two research coordinating centers will aid each site in completing requisite approvals. During the kick-off at the start of each wave for each site, ASAP-staff and the LSI will agree upon a schedule of meetings, which will include a scheduled meeting (likely once/month) and how best and when to convene ad hoc meetings. Calling an ad hoc meeting may be prompted based on the data monitoring where there is an unfavorable mismatch between the number of patients admitted who were eligible for the ASAP protocol and those who received it. For example, a site may have had 15 Veterans admitted who could have benefited from the ASAP protocol, whereas only 3 Veterans received it. In this example, the mismatch may be because of logistical concerns implementing the project or because the site where research is being conducted is not fully engaged. ASAP personnel will communicate about these concerns and, as necessary, perform a Plan-Do-Study-Act (PDSA) to determine how to improve implementation of the ASAP protocol. Should it be determined that a given site is not engaged in the project, Drs. [name] and [name] will communicate with the Director to provide notification and to seek guidance on next steps.

In order to keep all 6 engaged intervention sites informed of changes to the protocol, informed consent, and/or HIPAA authorization, Drs. [name] and [name] will send emails out to the LSI and appropriate local staff (e.g., site-based research assistants) regarding upcoming changes as well as the most updated forms. Should questions arise regarding updates, [name] has the contact information (including email addresses, VA-office phone number, and cell phone numbers) of each LSI. As such, an ad hoc meeting could be convened to discuss changes. Additionally, announcements regarding any changes will also be made on the Systems Redesign Virtual Collaborative/IOP. These same lines of communication will also be used to inform local sites of any serious adverse events, unanticipated problems, and/or interim results which may impact the conduct of the study. Sharing unanticipated problems as well as possible solutions is an important component of our Systems Redesign Virtual

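### The open IOP hub and the Section 6 lines to all six sites are not tied to kick-off, so site-periods coded as control may see outcome data or ASAP materials; if that raises testing early, the effect is understated

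*Protocol*

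**What the plan says.** Section 5.1.c (Protocol) describes the Integrated Operations Platform thus: "it is a web-based tool that is openly accessible (no passwords required". On its audience: "The IOP hub will serve the ASAP project as a connectivity hub for investigators, site PIs, systems redesign personnel, and VHA operational partners". On its content: "Resources including staff education materials, articles, protocols, and project charters will be shared in the library". Under Data Monitoring the same section adds: "The hub will include facility-level data for: OSA diagnosis and ASAP primary and secondary effectiveness outcomes", and then: "The hub allows sites to compare their data to other sites and to examine trends over time".

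Section 6 sets up a second route. Its stated purpose begins: "In order to keep all 6 engaged intervention sites informed of changes to the protocol, informed consent, and/or HIPAA authorization". The means are emails to local investigators and staff, and in addition "announcements regarding any changes will also be made on the Systems Redesign Virtual Collaborative/IOP". The same lines are then to be used to "inform local sites of any serious adverse events, unanticipated problems, and/or interim results which may impact the conduct of the study". The section closes the topic by naming learning between sites, and from interim results, as a benefit.

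Other components are limited to sites past kick-off. Section 5.1.c confines the Virtual Collaborative and its monthly calls to active sites and sends chart-review results to implementation sites. Section 5.1.d confines the monthly audit and feedback in the same way.

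Section 5.7.b codes every site-period as control or intervention and counts only active implementation as intervention. Waiting periods are therefore control. The timing sensitivity analysis in Section 5.7.c only moves the start of intervention later.

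**The concern.** Section 5.7.a prefers the stepped wedge to a before-after comparison because underlying diagnosis rates may drift. The randomised part of that protection is the contrast between sites that have crossed over and sites still waiting. The external control sites also inform the time trend, but they are matched, not randomised.

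Data monitoring is one of the two named components of the intervention, and Section 5.1.d counts hub visits as sites auditing their own performance. Comparative outcome data on an open hub are therefore intervention content. If a waiting site sees that a Wave 1 site has raised its testing rate and acts on it, its control periods are partly treated. The planned model has no term for this, and the planned timing analysis looks in the other direction. At stake is the size of the reported effect and the cleanness of the randomised comparison.

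**Working it through.** **Inputs from the protocol.** Six sites, two per step, three 7-month active periods per wave, about 64 patients per site-period, control rate 7%, between-site CV 0.3, 0.5 or 0.8, two-sided 0.05, 30 control sites. The model has categorical time, a random site intercept, an intervention-site indicator, and active and sustainability terms.

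**Assumptions.** Figure 1 is not available, so the layout is assumed. Section 5.7.b speaks of 8 periods (starts taken as periods 4, 5 and 6). The 3.5-year span gives 42/7 = 6 periods (starts taken as 2, 3 and 4). Uptake f, the share of the full effect reached by an exposed site before kick-off, is not in the protocol; I use 0.10, 0.25 and 0.50. The work is on the linear scale that suits the power table, so the figures are approximate for the planned generalized linear mixed model.

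**Step 1: reproduce Table 3.** Generalised least squares on site-period proportions, within-cell variance 0.07 × 0.93 / 64, between-site SD = CV × 0.07, power = Φ(δ/SE − 1.96). With six sites and 6 periods, 7% versus 15% gives 0.951 / 0.935 / 0.925 for the three CVs, against 0.95 / 0.93 / 0.93 in Table 3. All 12 active-versus-control cells agree within 0.005. With 8 periods the row is 0.962 / 0.955 / 0.951.

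**Step 2: weight of the waiting periods.** The estimator is a weighted sum of cell proportions. If waiting cells rise by f × θ, the expected estimate is θ × (1 + W × f), where W is the summed weight of the six waiting site-periods (Wave 2: one period × 2 sites; Wave 3: two periods × 2 sites).

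- Six sites only, either layout: W = −1.00.
- 30 unexposed controls, 8 periods: W = −0.27. The control sites' cells from Wave 1 kick-off onward carry the other −0.73.
- 30 unexposed controls, 6 periods: W = −0.50 to −0.51.
- 30 controls exposed as much as the waiting sites: the two sets of weights add to −1.00.

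**Step 3: estimate at f = 0.10 / 0.25 / 0.50 (CV 0.5).**

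| Scenario | Powered 8 points | Hypothesised 63 points |
|---|---|---|
| 8 periods, controls unexposed | 7.8 / 7.5 / 6.9 | 61.3 / 58.8 / 54.6 |
| 6 periods, controls unexposed | 7.6 / 7.0 / 6.0 | 59.8 / 55.1 / 47.2 |
| Controls equally exposed | 7.2 / 6.0 / 4.0 | 56.7 / 47.3 / 31.5 |

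If only Wave 3's later waiting period is exposed (8 periods, controls unexposed), the retained shares are 0.991 / 0.977 / 0.954. With 24 controls in place of 30, and all six waiting site-periods exposed, they are 0.973 / 0.932 / 0.864, so W barely moves.

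**Step 4: power.** With 30 unexposed controls, power for 8 points stays at 0.997 or above in both layouts. If controls are equally exposed at f = 0.50, it is about 0.96 (8 periods) or 0.88 (6 periods). In the six-site contrast alone (8 periods, CV 0.5) it falls from 0.955 to 0.908 / 0.782 / 0.447, but that is not the planned primary model. At 7% versus 70% the smallest estimate is 31.5 points. Against the largest six-site SE found (0.0235) that is over 13 standard errors. Raising the within-cell variance to its maximum multiplies the SE by at most √(0.25/0.0651) = 1.96, which still leaves more than 6.

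**The case against.** The best reply is that web access is an operational matter. What could really move testing (kick-off, Collaborative, calls, facilitation, monthly feedback) is tied to active sites. Section 5.5.a lists IOP use beside the kick-off, and Section 5.1.c says the hub data are there to improve implementation, which presupposes a site that is implementing. What is left is passive viewing of a library and a dashboard. The control sites carry most of the comparator weight in the 8-period model, and the test is not in danger.

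Much of this stands. Exposure is partial and uptake is probably small. But the protocol does more than stay silent: it states open access, puts comparative outcomes on the hub, and addresses all six sites in Section 6. The Collaborative half of that line is closed to waiting sites by Section 5.1.c; the email and IOP halves are not.

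Three stronger readings are tempting and are not supported. First, a reader might infer that any bias must run toward no effect and cannot create a false positive. That holds only if exposure raises testing before kick-off and alters nothing afterwards. A waiting site that postponed testing until its kick-off, or took up the programme faster because of early exposure, would push the other way. Second, a reader might take the 8-period figure with unexposed controls as the ceiling. An open hub is equally visible to the control sites, and a 6-period layout roughly doubles W. Third, a reader might infer that all interim effectiveness results go to all sites. Section 6 limits them to results that may affect study conduct.

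**Conclusion.** The point holds as a cheap improvement to the plan; the trial's conclusion is not threatened. Two routes reach sites whose data count as control, and nothing ties them to kick-off. Provided exposure raises testing before kick-off, the estimated effect loses about 0.27 × uptake (8 periods, 30 unexposed controls), about 0.5 × uptake (6 periods), or the full uptake fraction if control sites are equally exposed. Uptake is unknown, the layout is assumed because Figure 1 is unavailable, and the calculation is linear. At the hypothesised 7% versus 70%, only the size of the reported effect is affected.

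**What to change.** State in Sections 5.1.c and 6 that site-comparison data and interim effectiveness results are released to a site only from its kick-off. Until then, send a waiting site only safety, protocol, consent and HIPAA notices, by the email route to local investigators that Section 6 already provides. Lessons from earlier waves still reach later sites at their kick-off.

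The IOP is an existing national platform, so the team may be unable to restrict a page. In that case, give comparative data to active sites through the monthly feedback and Collaborative calls and do not post them openly. Simply removing them would take a data-monitoring component away from active sites. Report pre-kick-off hub access by site from the monthly usage counts already planned in Section 5.1.d.

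Keep all waiting periods in the primary analysis. Without them the six-site model cannot separate the active effect from time, and the estimate would rest on the non-randomised controls.

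Cost: two sentences and one access or posting decision. No new data are needed, and sample size, alpha and model do not change. Waiting sites see shared material later, and active sites may lose on-demand viewing of the hub data.

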## **5.2 Recruitment Methods**

**5.2.a General Recruitment Overview** As the quality improvement intervention is applied at the facility-level, rather than at the patient-level, the primary unit of analysis for ASAP is at the facility-level. Therefore, given that all six sites have already agreed to participate, recruitment has been completed. The primary effectiveness outcome, evaluated at the facility-level, will be the proportion of patients at each site which undergo and complete diagnostic testing (30-day sleep apnea diagnostic rate) For this rate, the denominator includes all eligible patients at the participating facilities. Because the ASAP program focuses on providers and systems of care, patients will not be consented. Each local site R&D board will be requested to provide approval for research to take place at that location.

ASAP sites will change the standard practice for all eligible ischemic stroke and TIA patients such that the routine clinical experience will be to receive OSA diagnosis and treatment. In the same way that all ischemic stroke/TIA patients receive other guideline-recommended care, patients at ASAP sites will also routinely receive OSA diagnosis and treatment. Certainly, our goal is to encourage all eligible patients to accept the recommendation to receive OSA diagnosis and treatment and the degree of patient acceptance will be a key component of the implementation evaluation, however the concept of recruitment as would be applied in a patient-level clinical trial is not applicable to this facility-level stepped-wedge trial. Similarly, although a patient-level trial would include a detailed description related to participant selection, for this facility-level analysis, patient selection is considered in terms of the patients who will be included in the denominator for each of the effectiveness outcomes as described above. However, the treating provider will determine if any given patient has a contraindication to PAP.

For Health Care Providers, we will request a waiver of documented consent (for interviews). We will record a verbal acknowledgement that the interviews are being recorded. No Health Insurance Portability and Accountability Act (HIPAA) information is being requested or accessed.

For Veteran patient chart reviews, we will request a waiver of consent and a waiver of HIPAA authorization. This study implements standard of care treatment for all patients. We will request a waiver of documented consent for Veteran interviews.

